## Abstract

Healthcare workers (HCWs) are at increased risk of infection by the virulent severe acute respiratory syndrome coronavirus-2 (SARS-CoV-2). Though data exist on the positivity rate of the SARS-CoV-2 reverse transcription polymerase chain reaction (RT-PCR) test as well as COVID-19-related deaths amongst HCWs in South Africa, the overall infection rate remains underestimated by these indicators. It is also unclear whether the humoral immune response after SARS-CoV-2 infection offers durable protection against reinfection. This study will assess the SARS-CoV-2 seroprevalence amongst HCWs in the Eastern Cape (EC) and examine the longitudinal changes (rate of decay) in the antibody levels after infection in this cohort. Using a multi-stage cluster sampling of healthcare workers in selected health facilities in the EC, a cross-sectional study of 2250 participants will be recruited. In order to assess the community infection rate, 750 antenatal women in the same settings will be recruited. Relevant demographic and clinical characteristics will be obtained by a self-administered questionnaire. A chemiluminescent microparticle immunoassay (CMIA) will be used for the qualitative detection of IgG antibodies against SARS-CoV-2 nucleocapsid protein. A nested cohort study will be conducted by performing eight-weekly antibody assays (X2) from 201 participants who tested positive for both SARS-CoV-2 RT-PCR and serology. Logistic regression models will be fitted to identify the independent risk factors for SARS-CoV-2 infection. The cumulative SARS-CoV-2 infection rate and infection fatality rate among the frontline HCWs will be estimated. In addition, the study will highlight the overall effectiveness of infection prevention and control measures (IPC) per exposure sites/wards at the selected health facilities. Findings will inform the South African Department of Health’s policies on how to protect HCWs better as the country prepares for the second wave of the SARS-CoV pandemic.

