### 2.4. Study Instrument

The questionnaire for this study was purposively designed to capture data that are relevant to the study objectives, using validated measures from the World Health Organization (WHO) STEPwise tool [14], COVID-19 risk assessment tool [15,16], persistence of symptoms [17] and vaccine hesitancy survey tool [18]. The questionnaire comprises variables on demographics, exposure risks, vulnerability risks, prior SARS-CoV-2 PCR tests and results, COVID-19 symptoms and management, post-COVID-19 persistent symptoms, and perception about the COVID-19 vaccine.

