### 2.5. Independent Variables

The selection of the parameters (included in the questionnaire) is based largely on the body of evidence from international literature on factors that influence or increase the risks of acquisition of SARS-CoV-2, severe COVID-19 disease, humoral immune response, and perception about vaccines [3,5,9,15,16,18]. Trained research nurses (without any affiliation to the study sites) will measure the height, weight, and mid-upper arm circumference according to standard protocols and the body mass index will be derived.

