### 3.1. Primary Analysis (Point and Cumulative Seroprevalence)

Descriptive statistics (means ± standard deviations for continuous data and counts and proportions for categorical data) will be used to summarize the baseline (demographic and clinical) characteristics of the participants. Cumulative and point seroprevalence indicating the overall infection rate will be estimated. In addition, the case fatality rate per health facility will be estimated based on the total number of deaths of HCWs and the overall infection rate from this study.

The cumulative outcome (positive result obtained by either or both of SARS-CoV-2 RT-PCR and serology) will be described by fitting the univariate logistic model to examine the association with the individual covariates. In addition, multiple logistic regression models will be fitted to identify factors that are independently and significantly associated with the outcome measures. All variables will be included in the logistic regression model, then, variables with missing data will be excluded in the second model. Sensitivity analysis will be performed using complete data only, with an assumption that missing data would have occurred at random.

In addition, the symptom data will be correlated with the composite results of SARS-CoV-2 PCR and serology tests. An epidemiological curve will be constructed by including data of all infected HCWs with SARS-CoV-2 PCR-positive tests.

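### The rule to enter all variables lets prior PCR results and COVID-19 symptoms into the model for risk factors for infection

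*Protocol article*

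**What the plan says.** The Abstract gives the aim of the regression: "Logistic regression models will be fitted to identify the independent risk factors for SARS-CoV-2 infection". Section 3.1 defines the outcome as a "positive result obtained by either or both of SARS-CoV-2 RT-PCR and serology". It begins by "fitting the univariate logistic model to examine the association with the individual covariates", moves to multiple logistic regression, and gives this entry rule: "All variables will be included in the logistic regression model". A second model then leaves out any variable that has missing data. The section names neither a candidate list nor an exclusion.

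Section 2.4 lists what the questionnaire collects. Besides demographics, exposure risks and vulnerability risks, it covers "prior SARS-CoV-2 PCR tests and results, COVID-19 symptoms and management, post-COVID-19 persistent symptoms, and perception about the COVID-19 vaccine". Section 2.5, headed Independent Variables, refers to the questionnaire parameters as a whole. It says they were chosen for their bearing on acquisition of the virus and also on "severe COVID-19 disease, humoral immune response, and perception about vaccines".

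Three other statements bear on the point. Section 2.9 matches prior PCR results to serology to form the result categories. Section 3.1 adds a separate correlation of symptoms with the composite result. Section 3.2 relates antibody presence at baseline to disease severity.

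**The concern.** A model meant to find risk factors for acquiring infection should contain only variables that can precede infection. Taken together, Sections 2.4, 2.5 and 3.1 admit two kinds that cannot serve. Prior PCR result is part of the outcome definition. Symptoms, their management and persistent symptoms are consequences of the infection being modelled.

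Factors associated with infection are a main outcome (Section 2.12), and multiple logistic regression is the only method given for independent association. If the rule is followed as worded, the PCR term cannot be estimated and confirmed cases may drop out of the model. The adjusted odds ratios for exposure area, PPE and comorbidity may then no longer describe the risk of acquiring infection.

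**Working it through.** The protocol gives no figure to reproduce here. The check has two parts: what follows from the definitions, and how far the other odds ratios could move.

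**1. PCR as a covariate.** By the outcome definition, P(outcome positive | PCR positive) = 1. No record can be outcome-negative and PCR-positive, so that cell is empty and the maximum-likelihood odds ratio is infinite. By default Stata, the package named in Section 3, removes a binary term that predicts perfectly, together with the records it predicts. Those records are the PCR-confirmed cases.

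**2. Effect on other odds ratios.** All rates below are assumptions, not protocol figures. A simulation of 675,000 records (300 × 2250) used one binary exposure with prevalence 40% and a true odds ratio of 2.0. Composite positivity was 10%, 20% or 45%. In the base case symptoms occurred in 55% of infected and 10% of uninfected staff.

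| Model | Assumption | Fitted exposure OR |
|---|---|---|
| No post-infection covariate | – | 1.99–2.02 |
| Symptom covariate added | symptoms depend on infection only | 1.98–2.01 |
| Symptom covariate added | infected: 70% symptomatic if exposed, 45% if not | 1.42–1.79 |
| Symptom covariate added | uninfected: 20% symptomatic if exposed, 10% if not | 1.56–1.77 |
| PCR-positive records dropped | 50% of infections detected, regardless of exposure | 1.98–2.03 |
| PCR-positive records dropped | detection 60% if exposed, 40% if not | 1.31–1.36 |

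Every run had 0 records that were outcome-negative and PCR-positive.

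**3. Hand check.** Dropping PCR-positive records multiplies the odds of infection in each exposure group by the undetected fraction.
- Detection 60% v 40%: 2.0 × (1 − 0.60)/(1 − 0.40) = 2.0 × 0.40/0.60 = 1.33, in line with 1.31–1.36.
- Detection 50% in both groups: 2.0 × 0.50/0.50 = 2.0.

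For symptoms, the odds ratio within a symptom stratum is 2.0 times the ratio, exposed to unexposed, of P(stratum | infected)/P(stratum | uninfected).
- Infected 70% v 45%: 2.0 × 0.70/0.45 = 3.11 among the symptomatic and 2.0 × 0.30/0.55 = 1.09 among the rest.
- Uninfected 20% v 10%: 2.0 × 0.10/0.20 = 1.00 among the symptomatic and 2.0 × 0.90/0.80 = 2.25 among the rest.

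A model without an interaction returns one value between the two strata, as the table shows. If symptoms depend on infection alone, the ratio is 1 and the odds ratio stays at 2.0.

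**The case against.** The strongest reply is that the article never names PCR results or symptoms as covariates. The rule follows talk of individual covariates and of independently associated factors, and the Abstract speaks of risk factors. It can therefore be read as entering all candidate factors without stepwise selection. The items in question also have other roles: PCR builds the outcome, symptoms have their own correlation, and severity belongs to the antibody analysis. A full covariate list is commonly left to an analysis plan, which is not shown.

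The reply stands in part. The intended meaning may be the narrower one, and the absence of a list is no fault. But the point concerns a stated rule that goes wrong if followed, and Section 2.5 points to the wide reading. The symptom correlation is an addition and removes nothing from the regression.

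It can also be said that the second model drops variables with missing data, so PCR items might fall out because not everyone was tested. That depends on how untested staff are coded. The step selects by completeness, not by causal role: a symptom item answered by everyone would stay, and a genuine exposure item with a few blanks would go.

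Finally, the univariate models leave the crude odds ratios untouched, and a dropped PCR term would be visible in the output. Both are true and limit the harm, but neither gives a sound adjusted estimate.

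**Conclusion.** The concern holds in a limited form. The entry rule is too broad as worded: it admits a component of the outcome and consequences of infection into the infection model. Only the failure of the PCR-positive term is certain, because it follows from the definition. Bias in the other odds ratios is conditional on symptoms or PCR detection varying with exposure given infection status. Under the assumed rates a true 2.0 then became 1.31 to 1.79; without that dependence it stayed at 1.98 to 2.03. The Introduction says testing focused on symptomatic people, so detection was selective. Variation by exposure area is plausible but not shown.

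A reader might infer more than the article supports:
- **That all adjusted odds ratios are invalid.** The simulation shows they can be unaffected.
- **That adjusting for symptoms blocks the path from exposure to infection.** Symptoms follow infection and do not lie on that path; the problem is conditioning on a consequence of the outcome.
- **That estimates would be carried past 1.** No fitted value went below 1.31.
- **That at least 201 of 2250 staff (201/2250 = 8.9%) would be lost.** The 201 in Section 2.10 is a recruitment target that depends on willingness to take part, not a count of PCR-positive staff.

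**What to change.** In Section 3.1, limit the entry rule for the infection model to pre-infection factors already collected: demographics, facility and exposure area, exposure-risk items, and vulnerability items including BMI and comorbidities. State that prior PCR results, COVID-19 symptoms and management, and post-COVID symptoms are excluded from that model. Leave out vaccine perception as well, since it is not a risk factor for acquisition. The list should not assume items the article does not show to be collected, such as household exposure; Section 2.4 speaks only of exposure risks in general.

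Keep symptoms in the separate correlation already planned in Section 3.1, and severity in the antibody analyses of Section 3.2. The cost is a change of wording, with no new data and no change to sample size.

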Due to the high exposure environment of hospitals, accurate data on the cumulative infection rate amongst HCWs will add to the existing literature on SARS-CoV-2 transmission dynamics. Quantifying risk factors for infection amongst HCWs can be instructive for future prevention interventions. Reported inadequate PPE availability and use has been shown to significantly increase risk for infection [3,5]. Within the health facilities, high exposure clinical areas (Accident and Emergency, acute medical ward, and intensive care units) have been associated with increased infections compared to administration or support services [4]. In contrast, other studies have shown no difference between different staff roles, suggesting that most infections are acquired outside of contacts with patients, or outside of the hospital environment [6,7,8].

Having at least one co-morbidity in a HCW was shown to be a significant risk for acquiring COVID-19 in one study [7]. Outside of the health care environment, a general practitioners (GP) network study of 3802 SARS-COV-2 tests performed in the UK, showed significantly increased infections among males, age 40–64 years, black ethnicity, lower socio-economic status, chronic kidney disease patients, and the obese. Interestingly, smokers had a lower risk of infection. [9] (de Lusignan et al. 2020). It is unclear whether the risk factors for acquiring SARS-CoV-2 infection among HCWs in South Africa will follow similar socio-demographic patterns reported in the rest of the world.

Molecular testing (RT-PCR) of respiratory samples (naso/oropharyngeal swab, sputum, and bronchoalveolar lavage) is the recommended diagnostic modality for confirming acute SARS-CoV-2 infection [1]. The limitation of this test, however, is the significant proportion of false negative tests, resulting in under-estimation of true infection prevalence. Asymptomatic infection is also frequent, occurring in 46% (95% CI: 18.48–73.60%) of cases in one meta-analysis [10]. Testing strategies that focus on symptomatic individuals (as were adopted by the South African Department of Health [1]) will always under-estimate the true population burden of the disease and negatively impact on adequate planning of IPC measures for the country.

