### 2.2. Participants

The study population will include all categories of HCWs at the selected health facilities. Given the large number of HCWs (doctors, nurses, allied health workers, and administrative staff) in the regional (about 1400 staff) and tertiary (about 1500 staff) hospitals in comparison to those in the primary health care (about 120 staff), it is expected that the majority of the participants in this study will be recruited from the two large hospitals. Since this cross-sectional study aims to provide mass screening (using a SARS-CoV-2 serological test) for all HCWs, about 2250 HCWs are expected to take part in this study. The estimated number of participants per study site is proportional to the overall count of HCWs at each site. A total of 750 antenatal women will be recruited from the study sites to provide data on the community infection rate. The recruitment of HCWs is pre-stratified for inclusivity and is proportionate to the total head count of staff in each facility as shown in Table 1.

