### 2.3. Study Procedure

All HCWs will be eligible to participate in this study. Using a multi-stage cluster sampling technique, participants’ clusters will be categorized by the facility of employment (Table 1) and exposure areas. Participants will be conveniently sampled within each cluster. Every HCW in each cluster will be given an equal opportunity to be sampled into the study, and participation will be purely voluntary.

Participants will be recruited from the study sites concurrently in order to avoid time variations in the main outcome measures. For inclusivity, exposure areas are pre-defined in accordance with risk assessment by Iversen et al. [4]:High risk: Accident and Emergency unit, acute respiratory (person under investigation/COVID-19) wards and intensive care units (ICU).Intermediate risk: non-respiratory admission wards, outpatient departments (OPDs) and other clinical areas.Low risk: administration offices and other non-clinical areas.

Information about this mass screening will be disseminated through the departmental heads and clinical managers. Each working areas/unit will be allocated specific days to give allowance for those on duty as well as those off-duty to participate with minimal interruptions in patient care. Each participant will complete a self-administered questionnaire. In addition, medical records of deceased HCWs during the pandemic will be reviewed in order to estimate the case fatality rate of HCWs in the study sites.

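### Section 3.1 enters all variables in one logistic model, so the adjusted odds ratio for exposure area probably excludes risk acting through patient contact and PPE, and no planned estimate adjusts area for confounders only

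*Protocol article*

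**What the plan says.** Section 3.1 gives the covariate rule: "All variables will be included in the logistic regression model". A second model then leaves out those variables that have missing data, and no other removal is planned. The stated aim is that "multiple logistic regression models will be fitted to identify factors that are independently and significantly associated with the outcome measures". The same section also plans "fitting the univariate logistic model to examine the association with the individual covariates", so an unadjusted estimate exists for each factor.

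Exposure area is a predefined three-level factor in section 2.3. The high-risk level is Accident and Emergency, COVID-19 wards and intensive care. The intermediate level is other clinical areas. The last level reads "Low risk: administration offices and other non-clinical areas". Section 2.2 describes the staff as "doctors, nurses, allied health workers, and administrative staff".

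Factors associated with infection are a main outcome (section 2.12). The Abstract says that the study will show how well infection prevention and control works by exposure site or ward. The Conclusions say that infection rates by area might guide staff allocation.

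Section 2.4 names questionnaire domains, among them demographics and exposure risks, but no individual items. Section 2.5 says that the variables come from published risk factors and cites references 3 and 5 among others. The Introduction cites the same two references for this statement: "Reported inadequate PPE availability and use has been shown to significantly increase risk for infection".

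**The concern.** Working in a COVID-19 ward or in intensive care plausibly raises infection risk largely because staff there meet more infectious patients and have more occasions for PPE to fail. Contact and PPE then lie on the path from area to infection. A model holding all three answers a narrow question: does area matter among staff with the same contact and the same PPE experience? It does not say how much risk goes with working in that area.

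The rule in section 3.1 makes no distinction between confounders, factors on the pathway and near-duplicates of another factor. The output labelled as independently associated could therefore show little or no area effect when ward risk is real. That works against the Abstract's aim, because adjusting a ward odds ratio for PPE removes the very infection-control failures that a ward comparison should reveal.

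A second, smaller question is whether job category and area overlap so much at the administrative end that the model cannot separate them precisely.

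**Working it through.** The article gives no figure on this point to reproduce, so the check is a worked scenario. Only n = 2250 comes from the documents (section 2.2; Table 1 gives 1100 + 1000 + 75 + 75 = 2250). **All other inputs are assumptions.**

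**Assumed inputs**
- Patient contact: 10% / 50% / 90% of staff in low / intermediate / high areas.
- PPE failure: 10% / 25% / 45%.
- Log odds of infection = −1.6 + 0.7 × contact + 0.6 × PPE failure + direct area effect. The direct effect for high versus low is either 0 or 0.4.
- Contact and PPE failure independent within an area, and no confounders. The estimate without contact and PPE therefore stands for the confounder-only estimate.

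**Part 1: high versus low area, no direct effect**

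Infection probabilities from the logistic formula are 0.168 (neither), 0.289 (contact only), 0.269 (PPE failure only) and 0.426 (both).

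- Low area: 0.81 × 0.168 + 0.09 × 0.289 + 0.09 × 0.269 + 0.01 × 0.426 = 0.191; odds 0.235.
- High area: 0.055 × 0.168 + 0.495 × 0.289 + 0.045 × 0.269 + 0.405 × 0.426 = 0.337; odds 0.508.
- Odds ratio without contact and PPE: 0.508 / 0.235 = 2.16.
- Odds ratio with them in the model: exp(0) = 1.00.

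**Part 2: the same with a direct log odds ratio of 0.4**

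The high-area probabilities become 0.232, 0.378, 0.354 and 0.525.

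- High area: 0.055 × 0.232 + 0.495 × 0.378 + 0.045 × 0.354 + 0.405 × 0.525 = 0.428; odds 0.749.
- Odds ratio without contact and PPE: 0.749 / 0.235 = 3.18 (unrounded odds).
- Odds ratio with them: exp(0.4) = 1.49.

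Simulated surveys of 2250 staff (200 per setting) agree:

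| Direct log OR | Area only: OR, share significant | Plus contact and PPE: OR, share significant |
|---|---|---|
| 0 | about 2.1 to 2.2, 100% | about 1.0, about 5% |
| 0.4 | about 3.2, 100% | about 1.5, 62% to 74% |

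**Part 3: job category beside area**

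Further assumptions: 12% doctors, 45% nurses, 13% allied, 30% administrative; 35% of clinical staff in high-risk areas; a varying share of staff breaking the link between administrative job and low-risk area. If the link is exact, the matrix of intercept, two area terms and three job terms has rank 5 of 6, so low-risk contrasts cannot be separated from job. Otherwise, with no direct effect:

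| Share breaking the link | SE of high v low log OR, area only | SE with job added | Ratio |
|---|---|---|---|
| 2% | 0.133 | 0.373 | 2.8 |
| 5% | 0.132 | 0.244 | 1.8 |
| 10% | 0.130 | 0.184 | 1.4 |
| 20% | 0.128 | 0.145 | 1.1 |

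At 1% some fits failed. From 2% upward, adding job left the odds ratio near its unadjusted size (2.06 to 2.19 against 2.12 to 2.16), so the cost is precision. High versus intermediate is not affected in this way: a separate run of 200 surveys per setting gave a median SE of 0.115 without job and 0.116 with it at 2%, because clinical staff of every category work in both areas.

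**The case against.** Much of the opposing case stands.

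- **The items are inferred.** Contact, PPE and job category are not listed as questionnaire items or model terms, and a full covariate list may sit outside the article. A reader might take it as stated that PPE enters the model. The documents support only a probable reading, through the exposure-risk domain and the shared references 3 and 5.
- **A crude ward contrast survives.** A reader might infer that ward risk disappears from the study's results. It does not: section 3.1 plans univariate models, and the Conclusions rest staffing on infection rates by area, not on adjusted odds ratios. What is at risk is the result labelled independent.
- **Job does not define area.** A reader might infer that area effects become non-estimable. That needs almost exact coincidence of administrative job and low-risk area. The low-risk level also takes in other non-clinical areas, and the article gives no job-by-area table.
- **The scenario partly returns its inputs.** The adjusted odds ratios of 1.0 and 1.5 are the assumed direct effects. The exercise shows how far the two estimands can differ, not what this survey will find.
- **Conditional association is the stated aim.** No total effect of area is claimed in section 3.1. But the Abstract's conclusions by ward need an estimate that keeps the contact and PPE pathway.

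Two further inferences should not be drawn. The Introduction's remark that some studies found no difference between staff roles does not show how this study would read its own model. And section 2.5 says that nurses will "measure the height, weight, and mid-upper arm circumference according to standard protocols and the body mass index will be derived"; this reads naturally as height and weight serving as inputs to BMI, and collinearity among body measures would not bias the area effect.

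**Conclusion.** The concern holds in a limited form. The covariate rule is stated rather than left open, and it makes no provision for variables on the pathway from area to infection. If the questionnaire holds contact or PPE items, the adjusted area odds ratio is a residual effect. The crude estimates keep the pathway but are not adjusted for age, sex, comorbidity or facility. The quantity that matters for ward conclusions, area adjusted for confounders only, is not planned.

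The size depends on how much ward risk passes through contact and PPE, which the documents do not give. Under the stated assumptions the high versus low odds ratio falls from about 2.2 to 1.0, or from about 3.2 to 1.5. Overlap of administrative staff with the low-risk area is a possible further loss of precision, confined to low-risk contrasts.

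**What to change.** Amend section 3.1 as follows.

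1. Add a prespecified exposure-area model adjusted for confounders only (for example age, sex, comorbidity, household or residence, and facility), without contact or PPE variables.
2. Report contact and PPE effects from a separate model adjusted for area.
3. Tabulate job by area before entering both. If they nearly coincide, use a combined role-by-area factor or compare jobs within clinical areas. Job category need not be dropped outright, since it may precede ward placement and confound it.
4. Base statements about area risk on the model in step 1, and do not call an area unassociated with infection on the strength of a model that contains contact or PPE.

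The cost is a few sentences in the plan and one or two extra model runs on data already to be collected. The all-variables model can stay as a supplementary result, labelled as conditional on contact and PPE.

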## 3. Statistical Analysis

Data will be exported from Redcap to the STATA Version 15 (Stata Corp., College Station, TX, USA) and cross-checked for completeness and accuracy. Incomplete data will be re-verified, and where possible, the OHS and NHLS databases will be reviewed to maximize the chances that data for the main outcome measures are collated accurately. Multi-level analysis will be performed on all the participants; those with complete and incomplete results. Differences in the baseline (demographic and clinical) characteristics of the two groups will be compared by using Pearson chi-square and Fisher’s exact test for bivariate analysis.

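### The second risk-factor model drops every covariate with missing data, and the complete-data sensitivity analysis is a weak check on it, so the adjusted odds ratios can be biased

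*Protocol article*

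**What the plan says.** Section 3.1 sets the aim of the adjusted models: "multiple logistic regression models will be fitted to identify factors that are independently and significantly associated with the outcome measures". It then fixes how incomplete variables are treated: "All variables will be included in the logistic regression model, then, variables with missing data will be excluded in the second model". The last step is: "Sensitivity analysis will be performed using complete data only, with an assumption that missing data would have occurred at random".

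The opening of section 3 adds some context. Incomplete data are to be re-verified, and the occupational health and laboratory databases consulted to complete the main outcome data. It also says: "Multi-level analysis will be performed on all the participants; those with complete and incomplete results". Baseline characteristics of two groups, most naturally participants with complete and with incomplete results, are then compared by chi-square and Fisher's exact tests.

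No imputation or weighting is stated. Most of the covariates come from a form that participants fill in themselves (section 2.3): "Each participant will complete a self-administered questionnaire".

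**The concern.** Factors associated with infection are part of the first main outcome (section 2.12), and section 7 expects the findings by exposure area to inform how staff are allocated. Three features of the rule put those odds ratios at risk.

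1. The second model removes a variable because someone left it blank, whatever its role. There is no threshold and no exemption for confounders; read literally, one blank is enough.
2. The sensitivity analysis may be the same fit as the first model. If it is instead set against the second model, the two differ in both participants and covariates, so a difference cannot be attributed to either.
3. The assumption named for the complete-data analysis, missing at random, is not the condition under which that analysis gives valid odds ratios.

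**Working it through.** The plan gives no figure to reproduce here. The only document input is the sample size (section 2.2): "about 2250 HCWs are expected to take part in this study". The missingness rates and effect sizes below are assumptions.

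**Step 1. Dropping an incomplete confounder.** Assume a complete binary exposure x with true adjusted odds ratio 1.5, and a confounder c with odds ratio 2.5 and prevalence 0.40. Let P(x=1) be 0.5 if c=1 and 0.2 if c=0, and logit P(y=1) = −1.4 + ln(1.5)x + ln(2.5)c.

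- P(c=1 | x=1) = 0.4×0.5 / (0.4×0.5 + 0.6×0.2) = 0.625.
- P(c=1 | x=0) = 0.4×0.5 / (0.4×0.5 + 0.6×0.8) = 0.294.
- Infection risks for (x,c) = (1,1), (1,0), (0,1), (0,0) are 0.480, 0.270, 0.381, 0.198.
- P(y=1 | x=1) = 0.625×0.480 + 0.375×0.270 = 0.4015, odds 0.671.
- P(y=1 | x=0) = 0.294×0.381 + 0.706×0.198 = 0.252, odds 0.3365.
- Odds ratio without c = 0.671 / 0.3365 = 1.99, against a true 1.50.

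This does not depend on why c is missing. A simulation (600 replicates of n = 2250, c missing in about 15%) gave 1.99 to 2.00 under every mechanism tried. When c was missing completely at random, the complete-case model that kept c gave 1.51.

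Range: with the confounder's odds ratio at 1.25, 1.5, 2 and 2.5, the same formula gives 1.61, 1.71, 1.87 and 1.99. If c is unrelated to exposure (P(x=1) = 0.2 in both groups), it gives 1.47, so little changes. The harm requires that the dropped variable is a real confounder.

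**Step 2. Does the sensitivity analysis add anything?** A standard logistic fit uses only rows complete on every variable in the model. That is the usual software default and is not stated in the protocol. Under it, the all-variables model and a complete-data analysis with the same covariates use the same rows and the same terms; in the simulation their coefficients differed by exactly 0.

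**Step 3. Does missing at random justify complete-case odds ratios?** Let c be missing with a probability that depends only on x and y, both fully observed, so missing at random holds. The complete-case odds ratio for x is then

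OR × [P(obs | x=1,y=1) × P(obs | x=0,y=0)] / [P(obs | x=1,y=0) × P(obs | x=0,y=1)].

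- Missingness depends on x only (25% if exposed, 10% if not): the factor is (0.75×0.90)/(0.75×0.90) = 1. Simulated 1.50.
- Missingness depends on y only (25% if infected, 10% if not): the factor is (0.75×0.90)/(0.90×0.75) = 1. Simulated 1.49.
- Missingness depends on both (40% in exposed uninfected, 10% otherwise): 1.5 × (0.90×0.90)/(0.60×0.90) = 2.25. Simulated 2.26.
- The same 40% placed in the exposed infected instead: 1.5 × (0.60×0.90)/(0.90×0.90) = 1.00.

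The bias can go either way and needs joint dependence on exposure and outcome.

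**Step 4. Rows left in the all-variables model.** With k covariates each missing independently at rate m, 2250 × (1−m)^k rows remain:

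| k | m = 1% | m = 2% | m = 5% |
|---|---|---|---|
| 10 | 2035 | 1838 | 1347 |
| 20 | 1840 | 1502 | 807 |

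**The case against.** The best defence has four parts.

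- **The sensitivity analysis need not be a repeat.** A reader might infer that it tests nothing. The text does not support that as a flat statement. Listwise deletion in the first model is a software default, and the sentence order also allows a comparison with the second model. If the second model's covariates are refitted on complete rows, the fits can differ: in the joint-dependence example, 1.99 on all rows against 2.99 on complete rows. This objection stands. That comparison still leaves the dropped confounder out, however.
- **Complete-case analysis is more robust than it may look.** One might say that it needs missingness unrelated to the outcome given the covariates. For logistic odds ratios that is sufficient but not necessary; step 3 shows no bias when missingness depends on the outcome alone. Joint dependence is also not obviously likely: forms are filled in at recruitment and study results come within a month (section 2.9), so most participants would probably not know their serology result. Those with an earlier PCR result are an exception.
- **Section 3 contains safeguards.** Re-verification and the baseline comparison of complete and incomplete participants help to show who is missing. They do not change how incomplete covariates enter the adjusted models, and the database review is aimed at outcome data.
- **Detail may sit in an analysis plan that is not shown.** That would answer a complaint about missing detail. Here the protocol states the rule itself, and a plan that followed it would carry it forward.

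**Conclusion.** The concern holds and should be fixed. The firmest part is the second model: choosing covariates by completeness can bias adjusted odds ratios even when data are missing completely at random. The sensitivity analysis repeats the all-variables model if it uses the same covariates with listwise deletion; otherwise its comparison with the second model mixes two changes. Missing at random alone does not validate it.

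The scope is limited to the risk-factor odds ratios. A reader might infer that all the main outcomes are compromised, but seroprevalence and case fatality do not use this covariate rule. Nor do the documents support a predicted bias. They give no missingness rates and do not say which variables will be incomplete, so the odds ratios and row counts above show what can happen under stated assumptions, including independence across items.

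**What to change.** In section 3.1, and in the analysis plan that follows it:

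1. Delete the rule that excludes variables with missing data from a second model.
2. Name one covariate set in advance, chosen for its role as confounder or risk factor, and use it in every adjusted model.
3. In the main model, handle incomplete covariates by a method valid under the stated missing-at-random assumption. Multiple imputation that includes the outcome, facility, exposure area and all model covariates is one suitable choice.
4. Keep complete-case analysis with the same covariates as the sensitivity analysis. State when it is valid: missingness that depends on covariates only or on outcome only, and not jointly on exposure and outcome.
5. Report the number of participants in each model and the missingness of each covariate.

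The cost is a few changed sentences and some extra analysis time in the software already named. No new data are needed.
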